### Sample size and justification

Sample size calculation was based on improvement in global assessment of severity in a study using a similar design, except that it employed a mixed diagnostic group rather than moderate to severe primary depressive disorder [14], 90% power, 2 tailed difference at 5% significance, 20% loss to follow up was 52 per treatment group (104 in total). However, this study did not employ an intention to treat analysis and there was a 30 percent loss to follow-up; therefore, the sample size has been inflated by a further 43 percent to 74 per group (148 in total). A further correction is to be made for the variability in the individual treatment from the SDDT and treatment as usual. A multiplicative correction factor to the sample size estimate of 1.18 calculated from [1 +rho*r/(1-rho)] [48] where rho is the intraclass correlation of 0.051[49] and r is the number of patients from each community mental health team (CMHT) per treatment arm (3-4). Therefore, the sample size is 87 per treatment group (174 in total). Sample size calculations were checked against a study of in-patient delivered combined psychotherapy and pharmacotherapy versus treatment as usual for patients with chronic depressive disorder [15]. The primary outcome variable was the 17-item Hamilton Depression Rating Scale (HDRS) and patients were followed up for 12 months. At baseline the combined treatment mean (sd) HDRS was 25.6 (4.4) and for clinical management it was 23.5 (4.8). At 12 months the HDRS score was 5.9 (5.1) in the combined treatment group and 11.3 (10.5) in the clinical management group (intention to treat analysis). Using a 2-tailed students t-test, 90% chance of detecting a difference at 0.05 level, and an effect size of 0.65, 51 patients per group are required (102 in total). If a 20 percent drop-out is assumed, then 122 patients (61 in each group) are required. Using the correction factor of 1.18 previously justified results in a sample size of 146 (73 in each group). In line with the more conservative estimate of the power of the study our aim is to recruit 87 patients per treatment group (174 in total).

### Randomisation

Once baseline assessments are completed by the research staff, patient details are sent to a Clinical Trials Unit (CTU) by the trial secretary. The treatment to which a patient is assigned is determined by a computer generated pseudo-random code using random permuted blocks of varying size, created by the CTU in accordance with their standard operating procedure and held on a secure server. Patients will be allocated with equal probability to each treatment arm with stratification by Trust. Allocation of the patients to a treatment arm is conveyed by the computer to the trial secretary who relays this information to a secretary supporting the SDDT and the referring clinician who will be expected to organise the patient's care if allocated to treatment as usual. Only the trial co-ordinator and trial secretary have password access to the randomisation data and research associates performing outcome assessments will not have access to the patient's health service records.

### Blinding

The research associate responsible for performing the baseline and outcome assessments will remain blind to randomisation until data collection has been completed. Any cases of unblinding are recorded. Researchers performing follow-up interviews will guess which group the participant has been randomised to at the end of 12 months treatment. At the end of the study, these guesses will be compared against chance.

### Statistical analysis

Statistical analysis for quantitative measures will be on the 'intention-to-treat' basis and carried out by the research team in two stages. At the first stage, analysis will be focused on process measures. Differences at each time point and in changing patterns over time between the two treatment groups and amongst clinical sites will be examined. Results from such analysis will help us to identify possible covariates or confounders at the individual level or clinical level that may need to be adjusted for when comparing the primary of secondary measures between treatment groups. Mechanism of missing data on major outcomes will be examined by sensitivity analysis, to inform adequate imputation procedures. At the second stage, the HDRS of the primary measure as well as multiple secondary measures will be analysed separately and jointly. As all measures are taken longitudinally, multilevel models for repeated measures will be used [49]. Data of patients who dropped out or not completed follow-up measures will be analysed in the manor of last-observation-carried-forward in multilevel modelling. The core model for each measure will be two-level with individuals as level 2 units and time occasions as level 1 units. If random effects or large variation among clinical sites are detected in the first stage analysis, the core model will be extended to three-level with clinical sites at the top of the hierarchy as level 3 units to account for random effects among clinics. For analysing multiple measures (or multiple end points) simultaneously to investigate global change or multi-dimensional change of the intervention effects, the core model will also be extended to a three-level structure with measures at the bottom of the data hierarchy. All models will estimate the mean changes of measures from the baseline to the later time points for each treatment group, and differences in such changes between groups by interaction terms between time and treatment group in models, adjusting for possible confounders or covariates. For continuous measures with reasonably symmetric distribution, ordinary multilevel models will be used in the analysis. Otherwise, data transformation before model fitting will be considered. For count data with a long tail in the distribution, multilevel Poisson models will be considered [50]. For ordinal measures, multilevel multinomial models will be considered [51]. Descriptive and simple statistical analysis will be performed in SPSS and MLwiN [52] will be used for multilevel models analysis.

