### Outcomes

**Primary outcome **measures are:

1. Longitudinal change in the 17-item observer rated Hamilton Depression Rating Scale (HDRS) [23,28] from baseline to 6 and 12 months as well as follow up assessments at 18 and 24 months. The primary analysis will be change over the baseline to 6 and 12 months. The purpose of the analysis at 18 and 24 months is to determine if any change is maintained once the patient has been discharged from the specialist depression disorder team.

2. Change in global assessment of function [24] from baseline to 6 and 12 months as well as follow up assessments at 18 and 24 months.

**Secondary outcome **MEASURES ARE:

1. Change in self-rated depression: a) self-rated Beck Depression Inventory version 1 [29], a measure of cognitive symptoms of depression from baseline to 3, 6, 9, 12, 18 and 24 months; b) Personal Health Questionnaire [30] from baseline to 3, 6, 9, 12, 18 and 24 months, rating of depression severity according to DSM-IV criteria; c) Quick Inventory for Depressive Symptomatology self rated version [31] from 3, 6, 9, 12, 18 and 24 months, a 16-item screening/diagnostic questionnaire rating depression severity according to DSM-IV criteria. The last scale has the best established psychometric data for remission compared to the Hamilton Depression Rating Scale. The other two scales are widely used in clinical practice by general practitioners and psychotherapy services in England and Wales.

2. Euroqol 5 D [32] as a measure of quality of life and costs from health and social care and society perspectives measured at 6, 12, 18 and 24 months. Use of the EQ5 D will enable utility score sto be gained from the patients that may then be used in a cost utility analysis

3. Change in social adjustment [33], an assessment of social and occupational functioning from baseline to 6, 12, 18 and 24 months.

4. Patient satisfaction and relationship with the clinician(s) on a four part 9-item questionnaire based on two other questionnaires used frequently in depression studies: the Patient Satisfaction Questionnaire [34] and the Patient Doctor Relationship Questionnaire [35]. These will be measured at 6, 12, 18 and 24 months.

**Process measures**, which will not be utilised to determine the effectiveness of the interventions, but will be used to understand the processes that are taking place:

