1. At baseline care received will be audited against standards of care outlined in NICE Guidelines [8,20] according to a 4-point scale (1 = not followed NICE Guideline, 2 = followed NICE Guideline< 50% of the time, 3 = followed NICE Guideline > 50% of the time, 4 = fully followed NICE Guideline) by an independent clinical expert. This assessment will then be applied to each three month block of care during the 12 month follow-up.

2. The number of patients with unrecognised axis 1 and 2 psychopathology [24] and medical co-morbidity will be recorded by the research team and also audited against treatment notes to determine if the specialist team is more accurate in terms of diagnosis.

3. At baseline life events and difficulties in the preceding 6 months and at 6, 12, 18 and 24 months after baseline will be recorded using the Brugha 12-item life event checklist [36]. The recognition or not of these life events and difficulties according to case notes will be audited in the two treatment groups.

4. At baseline social support in the preceding 6 months and at 6, 12, 18 and 24 months after baseline will be recorded using the 3 item social support and social network measure [37], which examines such support networks. The recognition or not of this social support according to case notes will be audited in the two treatment groups.

5. Adherence to medication [38], assessed at 6 and 12 months.

Quality of relationship between the patient and any secondary care mental health professional they have seen on a planned ongoing basis to manage their depression on a 9 item patient rated scale [35] assessed at baseline, 6 and 12 months.

6. Brief self-rated measures demonstrating the suitability of the cognitive therapy offered to the patient's needs: a) 18-item Others as Shamer Scale [39]; b) 22-item Forms of Self-criticising/attacking and Self-reassuring Scale [40]; c) 26-item How I act towards myself in difficult times scale [41]; d) 16-item Social Comparison Scale [42]; e) 16-item Entrapment Scale [43]; f) 16-item Defeat Scale [43]; g) 39-item 5 Facet Mindfulness Questionnaire [44].

7. At baseline, 6, 12, 18 and 24 months, participants' overall ruminative processes will be captured using the Rumination Scale [45]. Symptoms of rumination can predict vulnerability to depression, particularly relapse. As psychological treatments in the specialist mood team will aim to modify the ruminative process, this questionnaire will inform us whether this aim is being achieved.

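### The covariate screen allows the treatment comparison to be adjusted for process measures recorded after randomisation, some of which the intervention is meant to change

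*Protocol article*

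**What the plan says.** The Statistical analysis section of the protocol article sets out two stages.

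- Stage 1: "At the first stage, analysis will be focused on process measures". The comparison is described as follows: "Differences at each time point and in changing patterns over time between the two treatment groups and amongst clinical sites will be examined".
- Purpose of stage 1: "Results from such analysis will help us to identify possible covariates or confounders at the individual level or clinical level", namely those "that may need to be adjusted for when comparing the primary of secondary measures between treatment groups".
- Stage 2: all outcome models estimate the difference in change between groups "by interaction terms between time and treatment group in models, adjusting for possible confounders or covariates".

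The Outcomes section introduces the process measures as ones "which will not be utilised to determine the effectiveness of the interventions, but will be used to understand the processes that are taking place". It then lists them with their timing:

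- Medication adherence is taken at 6 and 12 months only.
- Concordance with NICE guidance is scored at baseline and again for each three-month block of the 12-month follow-up.
- Rumination is taken at baseline and at every six-monthly visit, with this rationale: "As psychological treatments in the specialist mood team will aim to modify the ruminative process".

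The Strengths section adds that, where mindfulness-based therapy is used, mindfulness and rumination should improve relative to treatment as usual.

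The same Statistical analysis section says the analysis is by intention to treat.

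**The concern.** A variable measured after randomisation and changed by the treatment is not a confounder of the treatment effect. If it lies on the path from treatment to outcome, conditioning on it removes the part of the effect that passes through it. If it also shares an unmeasured cause with the outcome, conditioning on it creates an association between arm and outcome that randomisation had excluded. In both cases the coefficient no longer estimates the intention-to-treat effect that the section promises.

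The screen makes this more likely. A process measure that diverges between arms during follow-up stands out in stage 1, and a likely reason for the divergence is that the specialist team moved it. At baseline, randomisation makes between-arm differences a matter of chance, so the screen is a poor guide to useful covariates there too.

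Guideline concordance shows what is at stake. The Design section recognises that the specialist team might succeed simply by delivering an acceptable standard of care. Adjusting for concordance during follow-up could remove that effect from the estimate.

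**Working it through.** **Step 1. Does the text admit follow-up values?** Stage 1 looks at differences at each time point and at change over time between arms. Change over time cannot be assessed from baseline data alone, so follow-up values are part of the screen. The purpose sentence and the stage 2 model sentence carry no restriction to baseline. Follow-up process measures can therefore enter the treatment comparison.

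**Step 2. Does the intervention aim to change any of them?** Rumination: yes, by the Outcomes section. Mindfulness and rumination: yes, by the Strengths section. Adherence has no baseline value, so any adjustment for it uses post-randomisation data. Concordance in the three-month blocks describes the care delivered after allocation. Life events, social support and unrecognised comorbidity need not be on the causal path.

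**Step 3. Reproduce the plan's figures (Sample size section).**

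- Effect size from the 12-month HDRS means and SDs: (11.3 − 5.9) / √((5.1² + 10.5²)/2) = 5.4 / 8.25 = 0.654, against 0.65 stated.
- Patients per group for 0.65, two-sided 5%, 90% power, t-test: 50.7, that is 51, as stated.
- Recruitment target: 74 × 1.18 = 87.3, against 87 stated.

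**Step 4. Simple illustration of lost power.** Inputs from the plan: 87 per arm, 20% loss, correction factor 1.18, d = 0.65. The mediated share m is not in the documents and is assumed.

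- Effective n = 87 × 0.8 / 1.18 = 59 per arm.
- Adjusted d = 0.65 × (1 − m).
- Power = Φ(d√(59/2) − 1.96), with √(59/2) = 5.43.

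| Assumed m | d | HDRS points (5.4 × (1 − m)) | d × 5.43 − 1.96 | Power |
|---|---|---|---|---|
| 0 | 0.65 | 5.4 | 1.57 | 94% |
| 25% | 0.4875 | 4.05 | 0.69 | 75% |
| 50% | 0.325 | 2.7 | −0.20 | 42% |

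This only shrinks d. It ignores the change in variance from adding a covariate that is correlated with arm.

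**Step 5. Simulation that includes that variance change.** Linear regression with and without one post-randomisation covariate, 51 analysed per group, 4,000 replicates. Assumed: a total effect of 0.65 SD and a shift of 0.65 SD in the process measure.

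| Assumed m | Adjusted effect (SD) | Power, adjusted | Power, unadjusted |
|---|---|---|---|
| 0 | 0.66 | 87% | 90% |
| 25% | 0.49 | 67% | 91% |
| 50% | 0.33 | 43% | 90% |
| 75% | 0.16 | 21% | 90% |

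**Step 6. Collider case.** Assumed: no true effect, the process measure shifted by 0.65 SD, and an unmeasured cause loading u on both the measure and the outcome. The expected adjusted estimate is −0.65 × u²: −0.16 for u = 0.5 and −0.23 for u = 0.6. The simulation returned the same values, with two-sided rejection rates of 12% and 23% instead of 5%. Here the bias runs against the team; associations of the opposite sign would reverse it.

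**Step 7. Contrast with a baseline covariate.** A covariate unaffected by treatment, with the loading u = 0.5 on both covariate and outcome, left the estimate at 0.65 with 91% power. The problem is the timing of the covariate, not adjustment as such.

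**The case against.** The strongest reply is that the section commits to very little. It speaks of possible covariates that may need adjustment, names no process measure as a covariate and sets no selection threshold. That stands, and it excludes several stronger readings a reader might infer:

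- **That the primary comparison will be adjusted for mediators.** The text permits this; it does not prescribe it.
- **That the process measures are all mediators.** Life events, social support and comorbidity need not be. Most of the measures also have baseline values, which are legitimate covariates.
- **That the Outcomes section is flatly contradicted.** Its statement that process measures are ones "which will not be utilised to determine the effectiveness of the interventions" can be read as saying only that they are not effectiveness endpoints. A covariate is not an endpoint. Letting them shape the effectiveness model sits uneasily with that statement but is not a plain contradiction.
- **That covariates would be picked to suit the HDRS result, or with allocation unmasked.** Stage 1 screens process measures, not HDRS, and the section does not say whether group labels would be masked.

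Stage 1 also has a sound use: detecting variation among sites that would call for a three-level model.

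It can further be said that the final covariate list belongs in a statistical analysis plan, which is not shown. That is right about the list, and its absence is not the complaint. The protocol does state where covariates are to be found and on what comparison. An analysis plan that followed this would inherit the problem, and one that did not would depart from the protocol.

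**Conclusion.** The concern holds as a fault in what the protocol permits. Screening process measures for between-arm differences at follow-up is an unsound way to choose covariates for a randomised comparison, and no sentence keeps post-randomisation values out of the outcome models. If such values were used, the estimate would not be the intention-to-treat effect.

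The size and direction of the bias are unknown. They depend on the share of the effect carried by the chosen measures and on unmeasured common causes, neither of which the documents give. The power figures in the working illustrate those assumptions and do not predict this trial's result. The simple calculation and the simulation differ at a 25% share (75% against 67%) because the simulation uses fewer patients and allows for the variance change. Both show a material loss once a moderate share is mediated.

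**What to change.** Amend the Statistical analysis section as follows:

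- State that covariates in every treatment-comparison model are prespecified and measured before randomisation: the baseline value of the outcome, Trust, and any named baseline prognostic factors, which may include baseline process measures.
- State that covariates will not be chosen from between-arm differences.
- Keep the stage 1 check of variation among sites as the basis for moving to the three-level model.
- Analyse post-randomisation process measures only in a separately labelled process or mediation analysis. This also removes the tension with the Outcomes section.

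The cost is a wording change. No new data, visits or patients are needed.

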### Design

A pragmatic single blind randomised controlled trial (RCT) of a specialist depression disorder intervention versus treatment as usual will be conducted. Participants will be individually randomised with stratification by mental health trust and allocated to each group on a one to one basis. Eligible participants will be followed for 24 months. The primary outcome will be observer rated depressive symptoms over the first 12 months but further analysis will explore if any differences in outcome are maintained at 24 months, 12 months after the patient has been discharged from the specialist depression disorder team. Figure 1 shows the overall design of the study.

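### Carrying the last observation forward inside the multilevel model is unnecessary and can bias the HDRS effect, in a direction that depends on the dropout pattern

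*Protocol article*

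**What the plan says.** All statements on method are in the Statistical analysis section of the protocol article. For the longitudinal outcomes, "multilevel models for repeated measures will be used", with occasions nested in individuals. The treatment effect is read from "differences in such changes between groups by interaction terms between time and treatment group in models". The analysis set is intention to treat.

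Missing data are mentioned twice. One sentence says: "Mechanism of missing data on major outcomes will be examined by sensitivity analysis, to inform adequate imputation procedures". A few lines later comes the only named rule: "Data of patients who dropped out or not completed follow-up measures will be analysed in the manor of last-observation-carried-forward in multilevel modelling". No condition is attached to it, and it is not labelled as either a primary or a sensitivity analysis.

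The Outcomes section defines the primary HDRS analysis: "The primary analysis will be change over the baseline to 6 and 12 months". Months 18 and 24 have a separate purpose, which the Design section gives as: "further analysis will explore if any differences in outcome are maintained at 24 months".

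**The concern.** Last-observation-carried-forward (LOCF) assumes that a patient's score stops moving at the last attended visit. A patient lost before month 6 is then scored as unchanged from a baseline HDRS that had to be at least 16. The only HDRS course reported in the article, in Sample size and justification, shows large falls in both arms over 12 months, so a flat course is a poor default.

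The planned model does not need the device. Fitted by likelihood, it takes each patient's available visits and is valid under missing-at-random. The rule also sits awkwardly beside the sentence on the missing-data mechanism, because a method that is already fixed cannot be informed by that work.

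At stake are the size of the primary HDRS effect and, if retention differs by arm, its false-positive rate. The 18- and 24-month question is also affected, because a score carried from month 6 or 12 repeats the earlier difference.

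**Working it through.** **Inputs from the article (Sample size and justification).** HDRS mean (SD) in the in-patient study used to check the sample size:
- combined treatment: 25.6 (4.4) at baseline, 5.9 (5.1) at 12 months
- clinical management: 23.5 (4.8) at baseline, 11.3 (10.5) at 12 months

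Planned dropout is 20%. The other cited study, of similar design, lost 30%. The target is 87 per group.

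**The plan's own figure.** Pooled 12-month SD = √((5.1² + 10.5²)/2) = 8.25. Effect size = (11.3 − 5.9)/8.25 = 0.654, which matches the stated 0.65. A two-sided t-test at 5% with 90% power then needs 50.7, so 51 per group, as stated.

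**Effect on the planned contrast.** The model estimates a difference in change. Combined treatment changes by 5.9 − 25.6 = −19.7 and clinical management by 11.3 − 23.5 = −12.2, a difference of −7.5. If a proportion *d* of an arm is lost before month 6, for reasons unrelated to outcome, LOCF gives those patients zero change, so the arm's mean change becomes (1 − *d*) × true change.

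| Loss, specialist team / usual care | LOCF difference (true −7.5) |
|---|---|
| 20% / 20% | 0.8 × (−19.7) − 0.8 × (−12.2) = −6.0 |
| 30% / 30% | 0.7 × (−19.7) − 0.7 × (−12.2) = −5.25 |
| 10% / 30% | 0.9 × (−19.7) − 0.7 × (−12.2) = −9.2 |
| 30% / 10% | 0.7 × (−19.7) − 0.9 × (−12.2) = −2.8 |

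Equal loss shrinks the effect by the loss proportion. Unequal loss can move it either way.

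**No true effect.** Null bias = (difference in dropout) × (mean improvement), in favour of the better-retained arm. Rejection rates come from simulation: 87 per arm, baseline SD 4.6, 12-month SD 8.25, an assumed correlation of 0.3, and a t-test on change.

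| Loss | Improvement, both arms | Bias (points) | Rejection at nominal 5% |
|---|---|---|---|
| 20% / 20% | 12.2 | 0 | about 5% |
| 18% / 22% | 12.2 | 0.04 × 12.2 = 0.5 | about 6-7% |
| 15% / 25% | 6 | 0.10 × 6 = 0.6 | about 8% |
| 15% / 25% | 12.2 | 0.10 × 12.2 = 1.2 | about 15% |

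If both inputs are mild (18% / 22% and 6 points), the bias is only 0.04 × 6 = 0.24. Under the same settings, analysing observed data only gave no bias and about 5% rejection.

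**Loss spread over all visits.** A second simulation let dropout depend on the last observed score, which is missing at random, with visits at 0, 6, 12, 18 and 24 months. Trajectories, follow-up SDs and correlations were assumed. The true differences were −2, −4, −2 and 0 at 6, 12, 18 and 24 months.

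| Missing at month 12, specialist team / usual care | LOCF, 12 months (true −4) | LOCF, 24 months (true 0) |
|---|---|---|
| 22% / 22% | −3.3 | −0.7 |
| 31% / 31% | −3.1 | −0.7 |
| 11% / 31% | −4.6 | −2.05 (41% rejection) |
| 31% / 11% | −2.1 | +0.6 |

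Estimation without carried values, equivalent to a likelihood repeated-measures model, recovered the truth to within 0.06 points in all seven scenarios run, including three with no effect.

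**How the 24-month artefact arises.** If a fraction *p* of each arm is last seen at visit *k*, LOCF adds roughly *p* × (difference at visit *k*) to the 24-month difference. For patients last seen at month 12 that is *p* × (−4) here, although the true 24-month difference is zero. For patients never seen after baseline, no treatment difference is carried. In the unequal-loss rows this mechanism is mixed with the bias from unequal early loss.

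**The case against.** The sizes above rest on assumptions that can be called generous. The 12.2-point improvement comes from a study of in-patient treatment, whereas this trial recruits community and out-patient cases still depressed after at least six months of care. Usual-care improvement may be smaller. The article predicts no difference in dropout between arms, and placing all loss before month 6 exaggerates the effect, because later dropouts carry an on-treatment score. That stands, and is why the size is given as a range. Larger splits such as 10% v 30% (about 45% rejection with no true effect) are illustrations, not forecasts.

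The plan has also not ignored missing data: it promises to examine the mechanism. That is fair, but the article does not say how the promise changes the rule that patients will be "analysed in the manor of last-observation-carried-forward in multilevel modelling".

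Three stronger readings are tempting and are not supported.
- *Standard errors are too small because carried values count as data.* In the 12-month check with 20% loss in both arms, the model standard error (1.33) agreed with the empirical spread (1.34). With a true 5.4-point difference the LOCF standard error (1.44) exceeded that from observed cases (1.38). The harm shown is bias. The full multilevel model was not fitted with carried values, so its variance behaviour is untested.
- *LOCF raises false positives in general.* With equal loss and no true effect, rejection stayed near 5%.
- *LOCF builds maintenance into the 24-month data for everyone lost.* It does so only for patients lost after a post-baseline visit. Those lost before month 6 carry baseline, which dilutes a later difference.

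**Conclusion.** The point holds as a question of bias. The article fixes a missing-data rule that its own model makes unnecessary, that assumes no change after the last visit, and that is not reconciled with its neighbouring sentence. Because the method is stated, it is not a detail left to an unseen analysis plan.

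Under equal early loss of 20-30% the consequence is conservative: a 20-30% smaller effect. That still matters in a trial whose Weaknesses section concedes that it may be underpowered. Under unequal loss the direction depends on which arm is better retained, and a false effect of roughly 0.5 to 1.2 HDRS points is possible in the cases tabulated, smaller if both the imbalance and the improvement are modest. The 24-month conclusion is partly presumed for patients last seen at month 6 or later.

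Only the 20% and 30% losses, the HDRS means and SDs and the 87 per group come from the article. Splits by arm, timing of loss, correlations and intermediate trajectories are assumed. The rule should be corrected before analysis, because it bears on the primary estimate and the repair is cheap.

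**What to change.** Replace the LOCF sentence with one stating that the primary analysis is the planned multilevel model, fitted by (restricted) maximum likelihood to all observed assessments, with no carried-forward values at any visit, including months 18 and 24. Remove LOCF, or keep it only as a labelled sensitivity analysis.

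Add a sensitivity analysis for departures from missing-at-random. Delta-adjusted multiple imputation by arm is one suitable choice. State that the examination of the missing-data mechanism informs this analysis.

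The sample size of 174 and the data collection are unchanged. The cost is one sentence and a little extra analysis.

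### Trust, the stratification factor, has only data-driven routes into the outcome model, and no stated model carries the SDDT-clinician clustering that the sample size section implies

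*Protocol article*

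**What the plan says.** All references are to the protocol article.

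- **Randomisation:** "Patients will be allocated with equal probability to each treatment arm with stratification by Trust". The Design section says the same, and the sample section gives three trusts.
- **Statistical analysis, core model:** "The core model for each measure will be two-level with individuals as level 2 units and time occasions as level 1 units".
- **Statistical analysis, site level:** "If random effects or large variation among clinical sites are detected in the first stage analysis, the core model will be extended to three-level". The first stage is described as concentrating on process measures. Its results are also to suggest covariates, at patient or clinical level, for the outcome comparisons. Trust is not named among them, and the term for sites is not defined.
- **Sample size and justification:** "A further correction is to be made for the variability in the individual treatment from the SDDT and treatment as usual". The factor is 1.18, from an intraclass correlation of 0.051 with the community mental health team (CMHT) as the cluster and 3-4 patients per CMHT per arm.
- **Interventions:** SDDT patients are treated jointly by psychiatrists and cognitive behaviour therapists from one team; usual care comes from the referring teams. The number of SDDT clinicians is not given.

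**The concern.** There are two gaps between design and analysis.

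First, Trust is a known design factor, so no data are needed to decide whether it belongs in the model. The article makes its inclusion depend on what emerges in a first stage run mainly on variables other than HDRS, with no threshold for what counts as large variation. The primary model is then settled after looking at trial data, and two analysts could reach different models.

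Second, the sample size section accepts that treatment delivery induces correlation, but neither the core model nor its stated extensions has a level for the treating clinician. SDDT patients share clinicians with one another and usual-care patients do not share those clinicians, so this clustering is specific to one arm. A site effect common to both arms does not represent it.

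The precision of the primary comparison is at stake, with the two omissions acting in opposite directions.

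**Working it through.** **1. The plan's own figure.** Factor = 1 + rho × r/(1 − rho), with rho = 0.051:
- r = 3: 1.161
- r = 3.35: 1.180
- r = 4: 1.215

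So 1.18 lies within the stated r of 3-4, and 74 × 1.18 = 87.3 gives the stated 87 per group. The arithmetic reproduces. The design allows for clustering at 0.051; the core model contains none.

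**2. Omitting Trust.** Let Trust explain a share s of the outcome variance. Stratified 1:1 allocation removes that share from the true variance of the contrast, but a model without Trust leaves it in the estimated variance. True SE / model SE = √(1 − s), and the actual type I error is 2 × [1 − Φ(1.96/√(1 − s))].

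| s (assumed) | 1.96/√(1 − s) | Type I error |
|---|---|---|
| 0.02 | 1.980 | 0.048 |
| 0.051 | 2.012 | 0.044 |
| 0.10 | 2.066 | 0.039 |

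The error is mild and conservative.

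**3. Would the trigger fire?** The article names no test. As an illustration, a 5% one-way analysis of variance was simulated (4,000 data sets) on the outcome itself at ICC 0.051. It detects site variation with probability 0.47 for 3 trusts of 58 (174/3) and 0.29 for 25 CMHTs of 7 (an assumed layout: 3.5 per arm × 2 = 7, and 174/7 ≈ 25). The planned first stage looks mainly at other variables.

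**4. Ignoring SDDT-clinician clustering.** Assume k clinicians sharing 87 patients equally (m = 87/k), the 0.051 carried over from CMHTs to clinicians, and independent usual-care patients. The SDDT-arm design effect is DE = 1 + (m − 1) × 0.051. The variance of the difference is inflated by V = (DE + 1)/2, and type I error = 2 × [1 − Φ(1.96/√V)].

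| k | m | DE | V | True SE / model SE | Type I error |
|---|---|---|---|---|---|
| 3 | 29.0 | 2.428 | 1.714 | 1.309 | 0.134 |
| 6 | 14.5 | 1.689 | 1.344 | 1.159 | 0.091 |
| 9 | 9.7 | 1.442 | 1.221 | 1.105 | 0.076 |
| 12 | 7.25 | 1.319 | 1.159 | 1.077 | 0.069 |

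A simulation of 20,000 null trials per setting gave 13.0%, 9.0%, 7.6% and 6.8%. Over ICCs of 0.02-0.10 the extremes are 0.057 (ICC 0.02, k = 12: V = 1.0625) and 0.206 (ICC 0.10, k = 3: V = 2.40).

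The 1.18 does not offset this, because enlarging the sample does not correct the standard error that the model reports.

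**5. Price of modelling it.** With the inputs of step 4, Satterthwaite df = (DE + 1)² / [DE²/(k − 1) + 1/86]. For k = 3 this is 3.428² / (2.428²/2 + 1/86) ≈ 4.0, with t = 2.784 against 1.974 on 172 df. The interval is 2.784 × 1.309/1.974 = 1.85 times as wide as one that ignores clustering. For k = 6, 9 and 12 the ratios are about 1.27, 1.16 and 1.11.

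**The case against.** The strongest reply is that an article may leave the naming of a stratification covariate to the analysis plan, and that individual randomisation within Trust makes common Trust or CMHT effects largely cancel in the treatment contrast. The second part stands: step 2 shows that leaving out Trust costs a little precision and creates no false positives. The first part does not answer the point, because the article states a rule, and an analysis plan that follows it inherits the data-dependence.

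Four stronger readings are tempting and are not supported.

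- **That Trust can enter only through the detected-variation rule.** A first-stage covariate at clinical level is a second route. It too is chosen from the data.
- **That the quoted rule inflates the error rate to 13%.** The 7-13% comes wholly from clinician clustering, which that rule does not mention. It uses a CMHT-based ICC and an assumed number of clinicians. It also rests on a single-occasion comparison, where the plan models repeated measures, and on simple nesting, where joint psychiatrist-therapist care is a crossed structure. It further treats usual-care patients as independent.
- **That the detection step would usually miss real clustering.** No test is named. Under an assumed 5% test the chance is roughly even for three trusts and lower for CMHTs.
- **That a partially nested primary model is obligatory and nearly free.** Step 5 shows that its cost is heavy with very few clinicians, so whether it should be primary is a trade-off.

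**Conclusion.** The point holds in two parts of different weight.

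The firm part rests on the text alone: a known stratification factor is left to data-driven selection, and the form of the HDRS model is tied to a stage that concentrates on other measures. Its numerical effect is small and conservative, with type I error about 0.04-0.05 for a Trust share of 2-10% of the variance, itself an assumption.

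The conditional part is that the sample size section allows for treatment-related variability while no stated model carries SDDT-clinician clustering. An illustrative type I error is 7-13% for 12 to 3 clinicians at ICC 0.051, and 6-21% over ICCs of 0.02-0.10. The low end is close to nominal. The article gives neither the clinician number nor a clinician ICC, so this shows what could happen and does not estimate what will.

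**What to change.** 1. Include Trust as a fixed effect in every outcome model, without a test. With three trusts this uses two parameters, avoids estimating a variance from three units, and costs nothing in data collection.
2. Delete the condition that site variation must first be detected. If sites are meant to be something other than Trusts, define them and decide in advance whether they enter.
3. Prespecify at least a sensitivity analysis of HDRS with a random effect for SDDT clinician, or for psychiatrist-therapist pair, in the SDDT arm only (partially nested), with small-sample degrees of freedom. State how it relates to the 1.18 factor.

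The cost lies in the third item. Clinician identity must be recorded in a form usable for analysis; the article promises logs of SDDT assessments and discussions, and diaries of staff time, but does not say that each patient is linked to a clinician. Intervals in that analysis could be much wider: about 11% wider with 12 clinicians and about 85% wider with 3, under the assumptions above.
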